### Clinical assessment

A psychometric assessment will be performed by trained and independent psychiatrists to assess the following items.

Depression severity will be assessed using the French version of the MADRS (Montgomery and Asberg Depression Rating Scale) (51), a hetero-evaluation scale for depression. It is amongst the most widely used in everyday practice, comprising 10 items. The total score ranges from 0 to 60. Remission is considered to have been reached when the total MADRS score is less than 10.Anxiety severity will be evaluated using the French version of the BAS (Brief Scale for Anxiety) (52), a hetero-evaluation questionnaire evaluating anxiety intensity comprising 10 items: 6 for general symptoms and 4 for psychological symptoms. Each item is scored from 0 to 6 (53).Suicidal ideation and behavior will be examined using the French version of the C-SSRS (Columbia-Suicide Severity Rating Scale) (54). It assesses suicidal ideation for a given topic ranging from ‘wish to be dead’ to ‘active suicidal ideation with specific plan and intent.’ There are 5 closed questions on suicidal ideation, 6 questions on intensity, and 4 on suicidal behavior.

### PET assessment

The ^18^F-DPA-714 and ^18^F-FEPPA molecules are two second radiotracers that target TSPO (overexpressed microglial receptor with inflammation) (55, 56). These two tracers cross the blood-brain barrier (BBB) and have a good affinity for TSPO (57, 58). The ^18^F-DPA-714 tracer is metabolized rapidly and some metabolites secondary to oxidation can cross the BBB in small amounts (59). The FEPPA tracer is also metabolized but its hydrophile metabolites do not cross the BBB (57). The amounts of injected activity and the effective patient dose are comparable between the two tracers (47, 60–62). The ^18^F-DPA-714 tracer has been studied extensively in humans as well as in preclinical models (51 references on Medline) (46–49). There is less information on the use of FEPPA (14 references on Medline, only 8 clinical studies).

Articles on the FEPPA use in humans mention an acquisition time of 125 min, which is difficult to achieve with a large number of subjects and is very uncomfortable for patients who must be immobile during these 125 min. For FEPPA, the data analysis is performed on a kinetic model with two compartments and arterial blood samples must be collected from the patient to measure the input function of the radiotracer (62). The main advantage of using ^18^F-DPA-714 is its acquisition and analysis protocol. The radiotracer is injected (200 MBq) and then a 30-min acquisition is performed 1 h after the injection. The analysis consists of calculating a standardized uptake value (SUV). Some studies have shown that using this semi-quantitative analysis method and using a reference region results in less variability than studies using a kinetic model (49). Since ^18^F-DPA-714 appears to be the preferred tracer for studying neuroinflammation on PET, it will be used in this study.

In addition, there is known a genetic polymorphism for TSPO. This polymorphism determines the tracer′s affinity for TSPO, with some persons having high affinity sites, mixed affinity sites or lower affinity sites. The two radiotracers (^18^F-DPA-714 and ^18^F-FEPPA) are both impacted by this genetic polymorphisms (63). For feasibility reasons, the TPSO genotype of subjects cannot be an inclusion criterion; nevertheless, this parameter will be taken into account during the data analysis as a covariate, allowing us to weigh the PET imaging data based on whether the individuals have high or low affinity sites.

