### Outcomes

The primary outcome will be the TSPO density assessed by the volume of cerebral distribution of the tracer [18F]DPA-714 in the currently depressed group vs. the control group.

The secondary outcomes will be: (1) the TSPO density evaluated by the brain distribution volume of the [18F]DPA-714 tracer in the currently depressed vs. remitted depressed groups, (2) the clinical severity assessed by the Montgomery and Asberg Depression Scale—MADRS), BAS (Brief Scale for Anxiety), and the Columbia-Suicide severity rating scale—CSSRS), (3) MRI imaging: (i) structural (i.e., cortical thickness to quantify cortical atrophy); (ii) diffusion (i.e., the mean diffusivity for measuring microstructural integrity); (iii) T2^*^ relaxometry (i.e., the R2^*^ for measuring intracerebral iron content), and (iv) resting-state functional MRI (i.e., default mode network connectivity strength), (4) the concentrations of biological markers of peripheral inflammation (i.e., hs-CRP, IL-6, TNF alpha).

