#### Analysis of PET imaging data

To evaluate the brain kinetics of [18F] DPA-714, PET images will be co-recorded on the MNI atlas with PMOD® software. To construct time-activity curves of [18F] DPA-714, the PET images will be segmented into 13 regions of interest (ROI): precuneus, anterior cingulum, posterior, frontal, temporal, parietal, occipital cingulum, hippocampus, semi-oval centrum, anterior putamen, posterior putamen, caudate nucleus, and intersections, as defined in the MNI-AAL atlas. The binding potential (BP) is the ratio of B_max_ (receptor density) to KD (dissociation constant): BP = B_max_ / KD shall be calculated. Additionally, the distribution volume ratio (DVR) will be estimated from the region of interest and a reference region using, for example, Logan graphical analysis (66) with the cerebellum as reference region for the images obtained between 0 and 90 min (46). In this study, the DVR will be calculated as the slope of the linear part of the Logan analysis using PMOD software. We will calculate the BP for the 13 ROIs mentioned above, as well as for the entire brain.

For the primary hypothesis, PET data will be analyzed by multivariate ANOVA with TSPO Volume in the 13 ROIs as the dependent variables and diagnosis and genotype as fixed factors. Main effects will be considered significant at the conventional *P* ≤ 0.05. Effects in each region, will be analyzed by univariate ANOVA.

As a secondary analysis, a MANOVA including every brain region sampled (including all cortical and subcortical regions) will be performed to assess the effect of diagnosis on TSPO Volume. A partial correlation will be used in a secondary analysis to quantitate the relationship between TSPO Volume in the primary regions of interest and severity of symptoms of MDD measured by total MADRS score.

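### The primary PET endpoint is specified inconsistently: the 60–90 min SUV scan cannot support the planned 0–90 min Logan analysis, and neither gives an absolute distribution volume

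*Protocol article*

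**What the plan says.** Five places in the protocol article bear on the primary PET measure.

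- **Introduction (objectives) and Outcomes.** The primary comparison is on a distribution volume: "The primary outcome will be the TSPO density assessed by the volume of cerebral distribution of the tracer [18F]DPA-714", currently depressed group against controls. No unit is given here.
- **PET assessment.** The only acquisition schedule in the article is that "a 30-min acquisition is performed 1 h after the injection", with SUV as the read-out. The short scan and simple analysis are presented as this tracer's main advantage. For the tracer not chosen, the section notes a 125-min scan and that "arterial blood samples must be collected from the patient to measure the input function of the radiotracer".
- **Experimental procedures, Table 1.** Blood is drawn at the enrolment visit. No sampling is listed for the visit at which PET is done.
- **Study sample calculation.** The 80% power with 20 per group refers to a distribution volume of 12.3 vs 9.3 ml/cm³, measured with the other tracer.
- **Analysis of PET imaging data.** Time-activity curves are built in 13 regions. The DVR is the slope from "Logan graphical analysis (66) with the cerebellum as reference region for the images obtained between 0 and 90 min". A binding potential, defined as Bmax/KD, is also planned: "We will calculate the BP for the 13 ROIs mentioned above, as well as for the entire brain". The primary MANOVA then takes TSPO Volume in the 13 regions as its dependent variables. SUV does not appear in this section.

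**The concern.** The acquisition and the analysis describe two different experiments. A Logan plot works on activity accumulated since injection, and a scan that begins an hour later does not record that accumulation. The endpoint named in the objective and outcome is a third quantity, and the variable named in the test is not defined as any of them.

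This is the primary endpoint of a study recruiting through four centres. Early frames that were not acquired cannot be recovered later. If the window and the measure are not settled beforehand, the choice between an SUV measure and a DVR could fall after the data are available, and the stated power would belong to neither.

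**Working it through.** **Inputs.** Scan start 60 min, duration 30 min (PET assessment). Logan images 0 to 90 min, cerebellar reference (Analysis of PET imaging data). Means 12.3 and 9.3 ml/cm³, n = 20 per group, power 80% (Study sample calculation). Alpha 0.05, taken here as two-sided because sidedness is not stated. No SD is given.

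**1. The plan's own figure.** The difference is 12.3 − 9.3 = 3.0 ml/cm³. Without an SD the 80% cannot be reproduced, only inverted. By normal approximation for one two-group comparison:

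SD = 3.0 / [(1.960 + 0.842) × √(2/20)] = 3.0 / 0.886 = 3.39 ml/cm³.

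The exact t-test gives a standardised difference of 0.91 and an SD of 3.30. Over an assumed SD range of 2.5 to 4.5, power runs from 97% to 56% (normal approximation). All of this is in ml/cm³, a unit that neither SUV nor a unitless ratio shares.

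**2. Timing.** The scan covers 60 to 60 + 30 = 90 min. Acquired share: 30/90 = 33%. Missing share: 60/90 = 67%, all of it at the start.

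**3. Why the start matters.** With C_T and C_R the activity in the region and the cerebellum, the reference Logan plot is

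∫₀ᵗ C_T / C_T(t) = DVR × ∫₀ᵗ C_R / C_T(t) + constant.

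Both integrals run from injection. A toy two-tissue simulation shows what happens when they start at 60 min. Its rate constants are assumed and do not come from the document.

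| True DVR | Logan, 0–90 min data | Logan, 60–90 min data only | SUV ratio, 60–90 min |
|---|---|---|---|
| 1.25 | 1.20 | 1.28 | 1.28 |
| 1.5 | 1.40 | 1.54 | 1.54 |
| 2.0 | 1.75 | 2.01 | 2.00 |

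The truncated fit reproduces the late SUV ratio and not the 0–90 min Logan slope. The table does not rank the measures: in this toy model the full Logan slope itself sits below the true value. It shows only that they are different quantities.

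**4. Absolute volume.** DVR = volume in region / volume in cerebellum. Volumes of 6 and 4 give 6/4 = 1.5, and volumes of 9 and 6 give 9/6 = 1.5. A DVR therefore does not return an absolute volume, even from a full 0–90 min scan. That needs an input function.

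**5. Binding potential.** Reference Logan gives DVR − 1 (a DVR of 1.5 gives 0.5). It does not give Bmax/KD as a separately identified quantity.

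**6. Side by side.**

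| Quantity named | From a 60–90 min scan | From a 0–90 min scan, no input function |
|---|---|---|
| Distribution volume, ml/cm³ | no | no |
| SUV or late SUV ratio | yes | yes |
| Logan DVR, or DVR − 1 | no | yes |
| Bmax/KD, separately identified | no | no |
| TSPO Volume (MANOVA) | not defined | not defined |

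**The case against.** The strongest reply is that the PET assessment paragraph argues for a choice of tracer. It describes usual practice in the present tense, while the analysis section says prospectively what will be done in this study and presupposes 0–90 min images. The procedure for the assessment visit gives no PET timing. On that reading the DVR is computable, and a cerebellar reference means that it needs no arterial blood. This has weight: the document does not settle which section governs. It does not remove the conflict. The paragraph stands under the PET assessment heading, holds the only schedule given, and justifies the tracer by its short scan. If 0–90 min is intended, that justification has to be corrected.

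A second reply is that distribution volume is loose naming for DVR. That is possible in the objective and outcome, which carry no unit, but the sample-size text uses ml/cm³.

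A third is that an article condenses the full protocol. That explains omissions, and the silence of Table 1 on sampling at the PET visit is weak evidence by itself. It does not explain two incompatible specifications.

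Some stronger inferences are not supported:

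- **That the primary endpoint cannot be computed at all.** For the DVR this holds only if the scan is really limited to 60–90 min.
- **That every named quantity is a separate rival endpoint.** A binding potential from reference Logan is the DVR shifted by a constant and gives the same group test.
- **That the endpoint will be picked after the data are seen.** This is a risk, not something the document shows.
- **That a cerebellar ratio would shrink the contrast by a given amount.** The document has no cerebellar figures.

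**Conclusion.** The point holds as an internal inconsistency in the primary endpoint. The described scan supplies 30 of the 90 minutes that the planned Logan analysis names and supports only SUV or a late SUV ratio. Under either acquisition, the distribution volume in the objective and outcome, read as an absolute volume as in the power statement, is not obtained without an input function, and none is described. The variable in the primary test is linked to none of the measures.

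The timing conclusion rests only on the two stated windows and on the form of the Logan plot. The simulation illustrates it and is not needed for it. Which of the two acquisitions is intended cannot be determined from the article. The 80% power does not carry over directly to SUV ratio or DVR. What transfers is the standardised difference that 20 per group can detect, about 0.9, and nothing in the document shows what the contrast would be on either scale.

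**What to change.** Reconcile the objectives, PET assessment, Outcomes, Study sample calculation and Analysis of PET imaging data to one acquisition window and one named primary measure. Two versions are coherent:

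1. **Keep 60–90 min.** The primary measure is the ROI-to-cerebellum SUV ratio over that window. Remove the Logan DVR, Bmax/KD and distribution volume as study measures. This changes wording and analysis in all five places but adds no scanning. The downside is a semi-quantitative endpoint.
2. **Use 0–90 min dynamic images, if these are in fact acquired.** The primary measure is the DVR, with any binding potential stated as DVR − 1. The downside is scanner time, and the short-scan rationale in PET assessment must be corrected.

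In either case, replace TSPO Volume in the MANOVA with the chosen measure. State that the 80% power based on 12.3 vs 9.3 ml/cm³ is on a different scale and does not carry over directly.

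As a low-cost check, compare genotype-adjusted cerebellar SUV between groups. A ratio removes any increase shared with the reference region, and the size of such an increase is not known from the document.

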### Biological markers

The involvement of certain pro-inflammatory cytokines in MDD was highlighted in a meta-analysis by Dowlati et al. (64) and a recent literature review by Miller et al. (23). In these two articles, higher plasma concentrations of IL-6 and TNF-alpha were found in the MDD group than in the control groups without MDD.

The biological marker assessment will involve measuring the concentration of peripheral inflammation markers that are circulating cytokines including IL-6 and TNF-alpha, especially. For each research site, samples will be taken at the Clinical Investigation Center for all subjects.

Also, hs-CRP will be assayed on the pre-screening day as part of the usual follow-up of patients and as part of the enrolment visit for volunteers in the control group (exclusion criteria for volunteers in the control group showing hs-CRP levels > 5 mg/L indicating a significant inflammatory state). All the blood samples will be collected in the morning in order to limit the impact of circadian rhythm on the measurement of inflammatory markers.

The samples will be stored by the Clinical Investigation Centers associated with each expert center before being sent to the hospital departments involved in the determination of peripheral cytokine levels (IL-6 and TNF alpha) at the end of the study.

### Outcomes

The primary outcome will be the TSPO density assessed by the volume of cerebral distribution of the tracer [18F]DPA-714 in the currently depressed group vs. the control group.

The secondary outcomes will be: (1) the TSPO density evaluated by the brain distribution volume of the [18F]DPA-714 tracer in the currently depressed vs. remitted depressed groups, (2) the clinical severity assessed by the Montgomery and Asberg Depression Scale—MADRS), BAS (Brief Scale for Anxiety), and the Columbia-Suicide severity rating scale—CSSRS), (3) MRI imaging: (i) structural (i.e., cortical thickness to quantify cortical atrophy); (ii) diffusion (i.e., the mean diffusivity for measuring microstructural integrity); (iii) T2^*^ relaxometry (i.e., the R2^*^ for measuring intracerebral iron content), and (iv) resting-state functional MRI (i.e., default mode network connectivity strength), (4) the concentrations of biological markers of peripheral inflammation (i.e., hs-CRP, IL-6, TNF alpha).

### Risk benefit balance

No direct individual benefit can be expected for subjects participating in this study. The therapeutic modalities used in these patients will not be altered by their participation in the study or by the results. Strict compliance with the inclusion and exclusion criteria will ensure there are no foreseeable risks for persons participating in this study. The imaging modalities used (MRI and PET) do not involve any foreseeable risk when patients presenting a contraindication to one or other of these examinations are not included according to the aforementioned inclusion/exclusion criteria. The principal investigator must constantly monitor, assess, and document risks and ensure that they can be managed satisfactorily.

### Experimental procedures (Table 1)

#### Preselection

Patients in both the currently depressed and remitted depressed groups will be preselected during their medical follow-up within each participating research site. Investigators will inform the patient and answer all questions about the purpose, nature of constraints, foreseeable risks, and expected benefits of the present research. They will also specify the rights of the patient regarding research and will verify the eligibility criteria. A copy of the Information/Consent form will then be given to the patient. Healthy volunteers for the control group will be invited by phone to participate into the study by a Clinical Investigation Centre clinical research associate. A copy of the information leaflet will be sent to them, giving them sufficient time to consider their participation.

**Table 1 T1:** Summary of INFLADEP design.

	**Preselection**	**Enrolment visit D0**	**Assessment visit D7 (± 5 days)**
Patient information	✓	✓	
Collection of informed consent		✓	
Clinical examination^1^ – Validation of eligibility criteria		✓	
Collection of blood samples^2^		✓	
MRI examination			✓
PET examination			✓
Questions about concomitant treatments		✓	✓
Search for AE/SAE		✓	✓

1 *Clinical examination: discussion with doctor, MADRS, BAS, C-SSCR, MINI surveys*.

2 *To measure CRP levels in healthy volunteers and biological markers (TNF-alpha, IL-6), TSPO phenotype in all subjects, beta-HCG for women of childbearing age*.

#### Enrolment visit

After obtaining the subject′s consent, a clinical examination will be performed to verify the eligibility criteria of the potential study participants along with the collection of psychiatric and somatic history, and current treatments. This clinical examination will include MINI (Mini International Neuropsychiatric Interview) (Appendix 5), which consists of a short, structured clinical interview that allows investigators to diagnose past and current psychiatric disorders according to the DSM (65), which is an exclusion criterion for subjects in the control group. This visit will also involve conducting psychometric assessments (MADRS, BAS, C-SSCR).

A blood sample will be taken to measure hs-CRP levels (inclusion criterion for the control group). This sample will also be used to measure IL-6 and TNF-alpha if the subject is included in the study. All the samples will be taken in the morning to take into consideration, as much as possible, the effects of circadian rhythm on circulating inflammatory biomarkers. Thereafter, an appointment will be scheduled for the assessment visit depending on the availability of the subject and the different technical platforms, at 7 ± 5 days following the inclusion visit.

#### Assessment visit

A PET scan ([18F]DPA-714) and a multimodal MRI scan will be performed. The subjects will be taken to an imaging unit for an MRI examination of around 40 min duration. As a safety measure, the MRI technician will carry out the usual safety checks needed for this type of investigation. The subjects will then be placed on a table, with their head positioned to enable brain imaging to be carried out. After placing the subject′s head in the support inside the MRI scanner, the scanning sequences will be carried out. The subjects will be able to talk to the operator at all times by intercom. Subjects must in general keep still during the MRI sequences. If an abnormality is discovered, the investigator will inform the patient during a follow-up visit.

### Statistical analyses

The Clinical Investigation Center in Toulouse contributed to the design of the study. The latter also provides methodological support to the project.

#### Study sample calculation

The main objective is to compare the central neuroinflammation measured by the TSPO distribution volume assessed by PET among both currently depressed and control groups. To our knowledge, this is the first study using the [18F] DPA-714 as biomarkers of neuroinflammation in depression with this type of study design. So, we cannot calculate the power of the study. However, few studies of this type are available in the scientific literature. There are studies using other markers of inflammation, such as [18-F]FEPPA (45). In the absence of sufficient literature data on which to base the calculation, a population of 20 patients per group seems appropriate considering the size of neuroimaging studies in the literature. In addition, 20 patients per group will allow us demonstrating, with a power of 80%, a statistically significant difference in the distribution volume between patients with a major depressive episode and controls, in the event the measured volume is similar according to the markers (based on data from the Setiawan et al. study measuring a volume of distribution of 12.3 vs. 9.3 ml/cm^3^ in the medial prefrontal cortex).

#### Analysis of PET imaging data

To evaluate the brain kinetics of [18F] DPA-714, PET images will be co-recorded on the MNI atlas with PMOD® software. To construct time-activity curves of [18F] DPA-714, the PET images will be segmented into 13 regions of interest (ROI): precuneus, anterior cingulum, posterior, frontal, temporal, parietal, occipital cingulum, hippocampus, semi-oval centrum, anterior putamen, posterior putamen, caudate nucleus, and intersections, as defined in the MNI-AAL atlas. The binding potential (BP) is the ratio of B_max_ (receptor density) to KD (dissociation constant): BP = B_max_ / KD shall be calculated. Additionally, the distribution volume ratio (DVR) will be estimated from the region of interest and a reference region using, for example, Logan graphical analysis (66) with the cerebellum as reference region for the images obtained between 0 and 90 min (46). In this study, the DVR will be calculated as the slope of the linear part of the Logan analysis using PMOD software. We will calculate the BP for the 13 ROIs mentioned above, as well as for the entire brain.

For the primary hypothesis, PET data will be analyzed by multivariate ANOVA with TSPO Volume in the 13 ROIs as the dependent variables and diagnosis and genotype as fixed factors. Main effects will be considered significant at the conventional *P* ≤ 0.05. Effects in each region, will be analyzed by univariate ANOVA.

As a secondary analysis, a MANOVA including every brain region sampled (including all cortical and subcortical regions) will be performed to assess the effect of diagnosis on TSPO Volume. A partial correlation will be used in a secondary analysis to quantitate the relationship between TSPO Volume in the primary regions of interest and severity of symptoms of MDD measured by total MADRS score.

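### Outcome and power are stated as an absolute distribution volume, but the only volume-type estimator described is a ratio to the cerebellum, and the quantity in the primary test is undefined

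*Protocol article*

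**What the plan says.** The Outcomes section defines the endpoint as an absolute-type measure: "The primary outcome will be the TSPO density assessed by the volume of cerebral distribution of the tracer". The sample size section uses the same scale. It takes its effect from an earlier study with a different tracer, "measuring a volume of distribution of 12.3 vs. 9.3" ml/cm3 in the medial prefrontal cortex, and states 80% power with 20 per group provided the volume is similar for the two tracers.

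The section on analysis of PET imaging data describes something else. It gives a binding potential for the 13 regions and the whole brain, and adds that "the distribution volume ratio (DVR) will be estimated from the region of interest and a reference region". The ratio is formed "with the cerebellum as reference region", from images covering 0 to 90 min. It continues: "In this study, the DVR will be calculated as the slope of the linear part of the Logan analysis using PMOD software". The primary test is then a MANOVA "with TSPO Volume in the 13 ROIs as the dependent variables and diagnosis and genotype as fixed factors", with no statement of which of these quantities TSPO Volume is. The PET assessment section names a further candidate, a standardized uptake value (SUV), used with a reference region.

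**The concern.** An absolute volume in ml/cm3 and a ratio to the cerebellum are different quantities. The first can show a rise across the whole brain. The second shows only what the target region does relative to the cerebellum, because anything that changes both in the same proportion is divided out. The article does not state that the cerebellum is unaffected in depression.

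Two things are at stake. The stated power may not apply to the quantity tested. And if that quantity is the DVR, a null result could mean either no neuroinflammation or neuroinflammation that includes the reference region, with no described means of telling them apart.

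**Working it through.** **1. Which quantity is analysed?** Side by side:

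| Section | Quantity |
|---|---|
| Outcomes | distribution volume |
| Study sample calculation | distribution volume, ml/cm3 |
| PET assessment | SUV, with a reference region |
| Analysis of PET imaging data, estimation | binding potential; DVR to cerebellum |
| Analysis of PET imaging data, primary test | TSPO Volume, undefined |

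No section describes estimating an absolute volume. PET assessment mentions arterial sampling as a requirement of the other tracer and presents the simpler protocol as the advantage of DPA-714. Table 1 lists blood sampling at enrolment only, not at the PET visit. The DVR is therefore the most natural reading of TSPO Volume, but the text does not fix it.

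**2. The plan's own figure.** The 80% cannot be reproduced, because no SD is given. The SD it implies can be back-solved (two-sided alpha 0.05 assumed, two-sample t test, 20 per group):

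- difference = 12.3 − 9.3 = 3.0 ml/cm3; relative difference = 3.0/9.3 = +32.3%
- implied SD = 3.30 ml/cm3 (3.39 by normal approximation)
- standardized difference = 3.0/3.30 = 0.91
- relative SD = 3.30/9.3 = 0.355 of the control mean

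**3. What a cerebellar change does to the ratio.** With a proportional cerebellar rise k in depressed patients, the relative DVR contrast is (12.3/9.3)/(1 + k) − 1:

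- k = 5%: 1.3226/1.05 − 1 = +26.0%
- k = 10%: 1.3226/1.10 − 1 = +20.2%
- k = 20%: 1.3226/1.20 − 1 = +10.2%
- k = 32.3%: zero

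The values of k are assumptions; the article gives no cerebellar values. A fall in the cerebellum would enlarge the contrast instead.

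**4. Power on the ratio scale.** This needs the SD of the DVR, which is unknown. Two cases (noncentral t, 20 per group):

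| Cerebellar rise | Same relative SD (0.355) | Half that SD |
|---|---|---|
| 0% | 80% | about 100% |
| 5% | 62% | not computed |
| 10% | 42% | 94% |
| 20% | 14% | 43% |

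These refer to a single-region t test, not to the planned MANOVA.

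**5. Do the described analyses cover the cerebellum?** It is not among the 13 listed regions. The secondary MANOVA on all sampled regions and the group t-tests on marker maps could include it if run on SUV. If run on the DVR they could not, since the cerebellum's ratio to itself is 1 by construction. The one check on PET interpretation described, under Analysis of all data, concerns atrophy.

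**6. How precise would a cerebellar comparison be?** If cerebellar SUV had the same relative SD, the 95% half-width would be 2.024 × 0.355 × √(2/20) = 0.227, about ±23 percentage points. At half that SD it would be about ±11.

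**The case against.** A reader might infer that the outcome simply is the DVR and that any cerebellar change cancels the group difference. The article supports neither. The DVR is introduced as an additional quantity, Logan analysis is offered as an example of a method, and the MANOVA variable is never equated with it. Cancellation is complete only when the cerebellum rises as much as the target; smaller rises attenuate.

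A reader might also take 42% or 14% as the trial's real power. Those figures rest on assumed cerebellar shifts, a back-solved SD and an unchanged relative SD. PET assessment itself cites evidence that a reference region lowers variability, which would offset part of the loss. The article also says that power cannot really be calculated for this tracer, and makes the 80% conditional.

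The choice of cerebellum carries a citation, and a regional ratio suits a hypothesis about specific brain regions. A reference-region check could sit in a fuller protocol or analysis plan, so its absence from a journal article is not by itself a defect. Finally, a non-significant cerebellar test at 20 vs 20 would not show that the cerebellum is unaffected.

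All of this stands as a limit on the size of the problem. It does not remove the mismatch. The condition attached to the 80% covers a change of tracer, not a change from an absolute volume to a ratio, and both scales are in the article's own text.

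**Conclusion.** The concern holds in limited form. The stated outcome and power basis are on an absolute scale, the only volume-type estimator described is on a relative one, and the dependent variable of the primary test is not identified. That much rests on the text alone.

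The rest is conditional on the DVR being the quantity analysed. In that case the 12.3 vs 9.3 effect and its 80% power do not transfer, and the attenuation in step 3 follows by arithmetic for whatever cerebellar change exists. Whether there is any such change, and how much power it would cost, cannot be determined from the article.

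**What to change.** - State which quantity (absolute volume, DVR, binding potential or SUV) is the dependent variable of the primary MANOVA, and use that name throughout.
- Restate the 80% power as applying to an absolute distribution volume only, not to the DVR.
- Prespecify a between-group estimate, with 95% confidence interval, of cerebellar SUV from the same scans, with genotype in the model. Report it as an estimate, not as a pass/fail test.
- Repeat the regional group contrast on SUV as a sensitivity analysis.
- State that a null DVR result will not be read as absence of neuroinflammation unless the cerebellar interval excludes a relevant difference.
- While editing, reconcile the 0 to 90 min Logan window with the 30-min acquisition starting 1 h after injection in PET assessment.

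The cost is a small amount of extra analysis on scans already planned, and SUV is already named in the article. The drawbacks are that SUV may vary more than the ratio, and that the cerebellar interval at 20 vs 20 will be wide, so it may often leave the question open.
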